## 2. Methods

### 2.1. Study Design

This is a pragmatic, non-randomised, pre–post design study where six groups of up to 10 participants will start the intervention at different times. Each group will commence a baseline period lasting six weeks. Primary outcome measures will be administered in week 0 (−t_1_) of the baseline period and in week 6 (−t_2_) of the baseline period. The allied health professionals will conduct assessments using the secondary outcome measures during the baseline period, making recommendations for consideration at the case conference held with the resident’s usual General Practitioner. The prescribed allied health intervention/s will last a maximum of 36 weeks with primary outcome measures taken during the intervention period at 12 (t_1_), 24 (t_2_), and 36 (t_3_) weeks, then at 12 (t_4_) and 24 (t_5_) weeks post-intervention. The case conferences will take place in week 1 or week 2 of the intervention period. The timing of the secondary outcome measures will vary depending on the mix of interventions chosen by the allied health professional and the participant needs. See the Supplementary file for further details.

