### 2.2. Study Setting

The intervention will be conducted in a residential aged care home in Canberra, Australia, with a maximum of 60 residents.

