#### Action Falls Program

In addition to the allied health interventions for individual participants (described in Table 1), the intervention will also involve an organisational intervention through implementation of the Action Falls program [17]. An Action Falls checklist will be completed with each participant (and or carer/family member, as appropriate). The Clinical Liaison Manager, who will receive formal training in the implementation of the Action Falls Program, will oversee the completion of the checklist, which can be carried out by any member of the team or residential aged care staff once training is complete.

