## 3. Data Analysis

### 3.1. Quantitative Analysis

All statistical analysis will be conducted using R version 4.2.1 (23 June 2022) in Rstudio (version 2023.6.2.561). Baseline demographic and descriptive statistics will be summarised for each group prior to the intervention starting (control phase). Primary outcome measures will be collected twice in the control period at week 0 and week 6. Primary outcome measures will be collected every 12 weeks during the intervention (weeks 12, 24, and 36) and at 12 weeks and 24 weeks post-intervention for each group. Categorical data will be summarised using frequency statistics and will be visualised. Continuous and other numerical data will be visually explored and summarised using sample descriptive statistics, selected as appropriate based on apparent distributions. A mixed-effects model will be computed, with treatment stage (i.e., pre- vs. post-intervention) as a fixed effect and subject as a random effect. Sensitivity analyses will be conducted, which will impute missing data using the “mice” package (version 3.15.0) [34].

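### The two-level pre/post stage does not fit a design with three phases: on-intervention and follow-up visits are either left out or averaged together, and any underlying trend is mixed into the same coefficient

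*Protocol article*

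**What the plan says.** Section 3.1 of the protocol article fixes a mixed model "with treatment stage (i.e., pre- vs. post-intervention) as a fixed effect", with subject as the random effect. It names no term for visit, time since start, calendar period or group. Section 2.6 powers the same pre-versus-post difference.

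The schedule has seven measurement points. For baseline, "Primary outcome measures will be collected twice in the control period at week 0 and week 6". After the start, Section 2.1 places measures at "12 (t_1_), 24 (t_2_), and 36 (t_3_) weeks, then at 12 (t_4_) and 24 (t_5_) weeks post-intervention". Section 3.1 uses the same term for the last two visits: "at 12 weeks and 24 weeks post-intervention for each group".

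On the setting, "six groups of up to 10 participants will start the intervention at different times" (Section 2.1), all in one home: "The intervention will be conducted in a residential aged care home in Canberra, Australia, with a maximum of 60 residents" (Section 2.2). Besides the individual therapies, "the intervention will also involve an organisational intervention through implementation of the Action Falls program" (Action Falls Program). Table 1 adds training of food service staff. For physiotherapy, Table 1 describes 2 hours of exercise a week for 25 weeks, 50 hours in all, followed by maintenance.

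**The concern.** A factor with two levels cannot represent three phases, and the article does not say which visits form the second level. Its own use of the term points to t4–t5, which would leave the three on-intervention visits with no place in the model. The other natural reading, everything after the start, produces an average over partial exposure, full exposure and withdrawal. These are different estimands. Neither is the effect at the end of the intervention, and neither separates that effect from its persistence.

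Second, every baseline value of a resident precedes every later value. With no concurrent control in the model, ageing, season or changes in the home go into the stage coefficient. Decline in a frail population would hide a benefit; unrelated improvement would imitate one.

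This is a stated specification that does not match the stated schedule. An analysis plan that followed the text would inherit the problem.

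**Working it through.** **Inputs from the article.** Visit times (Section 2.1), counted from enrolment and assuming the full 36 weeks are used: baseline 0 and 6; intervention 18, 30, 42; follow-up 54, 66. SPPB parameters (Section 2.6): between-subject SD 2.5, SD of the effect between subjects 2, within-subject SD 1, between-group SD 2, expected effect 2.5, alpha 0.01. Exercise: 25 weeks (Table 1).

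**Assumptions, not in the article.** SPPB trend of 0.5–1 point per year; linear build-up over 25 weeks; a fade to half at t4 and zero at t5; starts 6 or 12 weeks apart; 6 groups of 8 (n = 48, that is 60 less 20%).

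**The plan's own figures.** With one pre and one post value, SE = √((2² + 1 + 1)/50) = 0.346, and two-sided power at 1 point is 0.62, close to the 0.63 in Table 2. The other rows do not follow from the same SE: the four rows imply 0.51, 0.48, 0.49 and 0.34 for 2.5, 2, 1.75 and 1 point. That is a separate matter. Below, only the SDs of Section 2.6 are used, not Table 2.

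**1. Pooling over phases.** Share of the full effect present at each visit:
- weeks 12, 24, 36: 12/25 = 0.48, 24/25 = 0.96, 1.00; mean (0.48 + 0.96 + 1.00)/3 = 0.813.
- adding 0.5 and 0 at t4 and t5: (0.48 + 0.96 + 1.00 + 0.5 + 0)/5 = 0.588.

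A full effect of 2.5 points would then appear as 2.5 × 0.813 = 2.03 or 2.5 × 0.588 = 1.47. By week 12, 24 of the 50 exercise hours are due.

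**2. Trend.** The mean baseline time is week 3. Bias = yearly trend × gap/52.

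| Visits counted as post | Mean week | Gap | 0.5 point/year | 1 point/year |
|---|---|---|---|---|
| t1–t3 | 30 | 27 | 0.26 | 0.52 |
| t1–t5 | 42 | 39 | 0.38 | 0.75 |
| t4–t5 | 60 | 57 | 0.55 | 1.10 |

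For the first two rows, 0.26/2.5 = 10% and 0.75/2.5 = 30% of the planned effect. The sign follows the trend.

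**3. Cost of separating the phases.** The variance per resident is 2² + 1²/2 + 1²/(number of post visits), treating the individual effect as common to all later visits:
- pooled t1–t5: √((4 + 0.5 + 0.2)/48) = 0.313
- intervention stage of a three-level factor: √((4 + 0.5 + 0.333)/48) = 0.317
- week 36 versus the mean of two baselines: √((4 + 0.5 + 1)/48) = 0.339
- week 36 versus one baseline: √((4 + 1 + 1)/48) = 0.354

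**4. Adding calendar time** (generalised least squares, same SDs, random group effects).
- With visit: within a resident, calendar time equals start date plus visit time, so only differences between six non-randomised groups identify it. The SE of week 36 versus the first baseline visit is 3.7 (6-week stagger) or 1.9 (12-week) with linear time. Merging the two baseline visits gives 1.3 or 1.1. With 12-week periods it is about 1.0–1.6.
- With three stages: take the build-up above, no fade and no trend at all. The intervention estimate falls from 81% of the effect to 37–38% (linear time) or 39–41% (12-week periods). A fully maintained follow-up effect appears as 7–14%. The time term absorbs the build-up.

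**The case against.** The strongest objection is that a pre–post study cannot be rescued by its model, and that the obvious repair is worse than the fault. A reader might infer that the staggered starts are being wasted and that calendar time should go into the primary model. Step 4 shows otherwise: beside visit it is nearly unidentified, and beside stage it removes much of a real effect. The interval between starts is not stated and group order is not randomised, so the stagger offers little. Drawing start groups at random would change the non-randomised design and, under Section 4, need an ethics amendment; it is not a wording change. All of this stands.

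Three further limits also stand. The article does not show that later groups are exposed during baseline: it gives no go-live date for Action Falls and describes a checklist completed with each participant. Contamination is possible, not established. Nor is durability wholly unaddressed: Table 3 counts falls separately during and after the intervention, and Section 3.1 plans descriptive summaries. It is the model coefficient that says nothing about it. Finally, the trend and the effect profile are assumptions, and the bias may run either way.

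None of this answers the core point. The stated factor has two levels, the schedule has three phases, and the article's own term fits only the last.

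**Conclusion.** The point holds as a mismatch between the stated model and the stated schedule. The ambiguity over which visits count as post follows from the text alone and needs no assumption. Its size does need them: 81% or 59% of the full effect under the assumed profiles, and 0.26–0.75 SPPB points for 0.5–1 point per year if post means t1–t3 or t1–t5. Fade-out matters only if t4–t5 are coded as post.

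The documents do not support the stronger reading that the estimate is inflated, or that a time term would make it unbiased. Separating the phases cures the pooling; it does not remove trend. Week 36 lies 39 weeks after mean baseline (42 − 3), so the same assumed trend still contributes 0.38–0.75 points there. That has to be stated as a limitation.

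**What to change.** In Section 3.1, replace the two-level stage with visit as a categorical fixed effect, or with a three-level stage (baseline −t1, −t2; intervention t1–t3; follow-up t4–t5). Under the visit model, name week 36 versus the pooled baseline as the primary contrast, and report t4–t5 versus baseline as a separate durability contrast. If three stages are preferred, say that the intervention estimate is an average over t1–t3, not the week-36 effect.

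Keep calendar time out of the primary model. Fit calendar-time-adjusted stage models as a sensitivity analysis only, with a warning that they can absorb build-up. State plainly that the pre–post estimate cannot be separated from underlying trend or from home-wide exposure.

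For falls, add a sensitivity analysis that ends the pre-period at the date Action Falls goes live in the home, wherever a resident's 12-month look-back overlaps that date. The date has to be recorded.

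Cost: wording in the analysis section and no new visits. With n = 48 and the SDs of Section 2.6, the SE is about 0.34–0.35 for week 36, or 0.317 for the intervention stage, against 0.313 for the pooled stage.

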### 3.2. Qualitative Analysis

We will purposefully sample participants, carers, aged care staff, and health professionals as described in the program evaluation. In-depth interviews will be conducted to elicit their thoughts, opinions, and experience of the intervention. All interviews will be transcribed verbatim, and a reflexive thematic analysis will be completed using a variation of Braun and Clark’s reflexive thematic analysis [35]. Field notes will be kept and reported from key members of the research team for the duration of the study recording key events, interactions, and justification of key decisions made.

## 4. Ethics Review

This study has been approved by [blinded for peer review]. Any unforeseen amendments to the study protocol will only be enacted after expressed written approval from the HREC. Any important changes to the protocol will result in an ethics amendment to be approved with notifications to the ANZCTR and key stakeholders (participants, families, and the aged care provider).

## 5. Discussion

The results of this study will provide information about the clinical, implementation, and effectiveness outcomes of this integrated transdisciplinary allied health services model (EAHOP intervention) for people living in residential aged care and those transitioning into residential aged care. The results will be used to develop evidence-informed guidelines for residential aged care providers on the delivery of allied health services. The economic evaluation will provide evidence to inform how allied health service provision could be provided in residential aged care.

## Figures and Tables

**Figure 1 healthcare-13-00341-f001:**
[figure not shown]
An integrated transdisciplinary allied health service model (EAHOP intervention).

**Table 1 healthcare-13-00341-t001:** Summary of interventions within EAHOP.

	Description
Occupational Therapy	Participants will identify goals relating to activities of everyday living with specific reference to self-care, leisure activities, and productivity that are meaningful to them that they would like to be engaged with and/or become more satisfied with. The occupational therapist will develop goal-directed and individually tailored occupational therapy interventions to improve performance and satisfaction with the identified occupational performance challenges. These will be discussed with Health and Lifestyle staff to support ongoing sustainable implementation with the individual.
Physiotherapy	Participants will engage in exercise based upon the SUNBEAM program [15] involving 2 h per week of individually tailored strength and balance exercises prescribed by the physiotherapist for 25 weeks (total 50 h) and then a maintenance program for the duration of the intervention. In some instances, participants may not be suitable for the SUNBEAM program. In these cases, they will be offered an individualised virtual cycling experience [16] once a week for the intervention’s duration.
Dietetics and Nutrition	Participants diagnosed with weight loss or at risk of malnutrition will be provided with an individualised, high-protein, high-energy diet by fortifying menu items such as porridge, soups, mashed potato, and desserts, and/or oral nutrition supplements. In addition, the dietitian will provide modified menus to Food Service staff and training to Food Service staff on how to fortify menu items as per modified menus.
Speech Pathology	Participants will receive individualised interventions focused on communication partner training over a period of up to 36 weeks. The speech pathology intervention may include communication repair strategies, an education component, role play, practice, and recording of communication interactions to identify and address communication challenges.
Optometry	Participants will receive an onsite, mobile assessment by an optometrist evaluating visual function (including refraction, confrontation fields, visual acuity, ocular structure (macula and optic nerve lenticular assessment, and intra-ocular pressure) to address visual impairments that may contribute to fall risk. Actions arising from the assessment of visual function may include new spectacle prescriptions or referral of participants for management of ocular disease.
Pharmacy	Participants will receive an onsite medication review by a pharmacist who will provide recommendations regarding the resident’s medication to the participant’s GP, nursing staff, and family members. After the initial medication review, participants will receive a 2-week follow-up visit to understand how medication decisions are implemented in the medication treatment and charts. Each participant will have an initial case conference and then a follow-up visit from the pharmacist every 3 months (online or in person).

**Table 2 healthcare-13-00341-t002:** Associated power based upon *n* = 50 and mean change in the SPPB.

Increase Mean Response After Intervention	Power
2.5	0.99
2	0.94
1.75	0.84
1	0.63

**Table 3 healthcare-13-00341-t003:** Outcome measure summary.

Primary Outcome Measures	
Falls: Number of falls in past 12 months Number of falls during intervention period Number of falls after intervention	
Quality of Life Aged Care Consumers (QOL-ACC) [19]	
Frailty: The Frail in Nursing Homes (Frail-NH) Scale [20] and the and Patient Health Questionnaire (PHQ9) [22]	
Short Physical Performance Battery (SPPB) [21]	
**Secondary outcome measures**	**Allied health discipline**
Short Falls Efficacy Scale—International (Short FES-I) [23]	Physiotherapy
Subjective Global Assessment (SGA) [24] Mid-arm muscle circumference [25,26] Quantitative analysis of dietary intake will be calculated before and after fortification	Nutrition and Dietetics
Canadian Occupational Performance Measure (COPM) [27]	Occupational Therapy
Number of medications (that contributed to increased risk of falls) ceased/changed at case conferences Number of case conferences and pharmacist follow-ups Rate of GP agreement on pharmacist recommendations	Pharmacy
Number of new or updated spectacles recommended Number of referrals arising from vision assessment The National Eye Institute Visual Functioning Questionnaire—25 (VFQ-25 + 10) [28]	Optometry
Holden Communication Scale [29] Number of communication breakdowns occurring The number of resolutions (strategies used to repair the communication breakdowns)	Speech Pathology
Revised Index for Social Engagement (RISE) [30]	All
Brief Pain Inventory (short form) [31] or PAINAD [32]	All
ACTION Falls: number of ACTION falls checklists completed [17]	All
Hospital leave days	All
Program satisfaction survey	All
Qualitative interviews	All
Program evaluation	All
Economic analysis	All

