#### 2.4.2. Case Conferencing

The allied health professionals will conduct their discipline-specific, secondary outcome measures during the baseline period and then make recommendations to be discussed at a case conference. The case conference will be attended by the resident’s General Practitioner, the research clinical liaison manager, and where possible the resident and family member. A plan of action will be agreed with the resident and their family following the case conference that could involve one or more allied health interventions depending on the needs of the resident.

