#### 2.4.4. Allied Health Professionals and General Practitioner

There are six allied health professionals, a dietitian, pharmacist, physiotherapist, occupational therapist, optometrist, and speech pathologist, who will conduct discipline-specific assessments and provide discipline-specific interventions as needed, as identified and agreed in the case conference with a General Practitioner assisting with the coordination of care.

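### The only outcome that counts fall-risk medicine changes is limited to case conferences, although Table 1 plans other routes by which medicines can change

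*Protocol article*

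**What the plan says.** **The outcome.** Table 3 lists three pharmacy measures among the secondary outcomes. The one that counts medicines is "Number of medications (that contributed to increased risk of falls) ceased/changed at case conferences". The other two are a tally of conferences and pharmacist follow-ups held, and the rate at which the GP agrees with the pharmacist.

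**The planned pharmacy contacts.** The Pharmacy row of Table 1 has the pharmacist review the medicines on site and give recommendations to the GP, the nurses and the family. It then says: "After the initial medication review, participants will receive a 2-week follow-up visit to understand how medication decisions are implemented in the medication treatment and charts". The row ends: "Each participant will have an initial case conference and then a follow-up visit from the pharmacist every 3 months (online or in person".

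**The conference.** Section 2.4.2 says of each discipline's clinicians that they "will conduct their discipline-specific, secondary outcome measures during the baseline period and then make recommendations to be discussed at a case conference". Section 2.1 adds: "The case conferences will take place in week 1 or week 2 of the intervention period". Section 2.4.2 continues: "A plan of action will be agreed with the resident and their family following the case conference". Section 2.4.4, which names the pharmacist, has the professionals "provide discipline-specific interventions as needed, as identified and agreed in the case conference".

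No section gives the week of the initial medication review. Section 2.1 says that the timing of secondary measures varies, and it refers to a supplementary file that is not shown.

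**The concern.** Table 1 describes pharmacy work that starts with a review and continues through an intervention of up to 36 weeks. Table 3 counts medicine changes at only one kind of event within that work. If a GP acts on a recommendation without waiting for the conference, or if a three-monthly visit leads to a medicine being stopped, the change is real but is not counted.

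The Discussion says that the results will inform guidelines for providers on delivering allied health services. A count that leaves out some of the changes would give those readers too low a figure for what the pharmacist's involvement achieved. Changes not recorded by date and route as they happen may be hard to reconstruct later.

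A second, weaker question is whether the two-week check is tied to the right event. Its stated purpose is to see how decisions are carried out, yet it is timed from the review and not from the conference at which plans are discussed.

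**Working it through.** **1. Which routes does the outcome cover?** The plan gives no figure to reproduce, so this step sets the two tables side by side.

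| Route in Table 1 (Pharmacy) | Counted by the Table 3 medicine-change outcome? |
|---|---|
| Initial case conference | Yes |
| Recommendation direct to GP, nurses, family | No, unless the change is made at a conference |
| Two-week visit | No |
| Three-monthly visits | No |

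The neighbouring outcomes do not fill the gap. A tally of contacts says nothing about medicines. An agreement rate is not tied to conferences, but agreeing to a recommendation is not the same as a medicine ceased, and a rate is not a number of medicines. No other row of Table 3 counts medicine changes.

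**2. How many planned contacts lie outside the conference?** Over 36 weeks, visits every 13 weeks give 2. Visits every 12 weeks give 2 if timed from a conference in week 1 or 2 (weeks 13 and 25, or 14 and 26), and 3 if timed from the start of the intervention (weeks 12, 24 and 36). The total is 1 conference + 1 two-week visit + 2 to 3 later visits = 4 to 5 contacts, of which 3 to 4 are not conferences. This counts contacts, not medicine changes.

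**3. How large is the undercount?** If a share *s* of changes is made outside conferences, the outcome records 1 − *s* of them. The documents do not give *s*. Taking *s* = 0.10 to 0.50 purely as an assumption, 0.90 to 0.50 of changes would be counted.

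**4. Timing of the two-week visit, conditional on a baseline review.** Let the review fall at *R*, uniform from week *a* to week 6 of baseline, and the conference at *C*, uniform over weeks 6 to 8 (intervention weeks 1 and 2). Uniform timing is an assumption. The visit is at *R* + 2, so it is uniform from *a* + 2 to 8. For *a* ≤ 4, a visit before week 6 always precedes the conference, and a visit in weeks 6 to 8 precedes it half the time:

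P(visit before conference) = (4 − *a*)/(6 − *a*) + ½ × 2/(6 − *a*) = (5 − *a*)/(6 − *a*).

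| Earliest review week *a* | P(visit before conference) |
|---|---|
| 0 | 5/6 = 83% |
| 2 | 3/4 = 75% |
| 3 | 2/3 = 67% |
| 4 | 1/2 = 50% |
| 5 | 25% |

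For *a* = 5 the visit is uniform over weeks 7 to 8. The probability is the mean of (8 − visit week)/2, which is 0.5/2 = 25%. A visit timed two weeks after the conference would fall in intervention week 3 or 4, after the conference in every case.

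**The case against.** **A conference count is a legitimate process measure.** The model is built around case conferencing, so what the conference yields is worth knowing. Table 3 also speaks of conferences in the plural and counts them, so a resident may have more than one. Both points stand, and they are reasons to keep the conference figure as one route. They do not make it a count of what the pharmacist's work changed overall.

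**Definitions may sit in the full protocol.** A journal article condenses, and data fields are commonly set out elsewhere. But this article does not leave the outcome open: it states a restriction to conferences, and that wording is what needs changing.

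**Two-week visit.** A reader might infer that the visit is simply mistimed and has nothing to check. The documents do not support that. The review is undated, and its placement in baseline is inferred from the general rule in sections 2.1 and 2.4.2. The share of visits before the conference runs from 83% down to 25% depending on when in baseline reviews begin, and a review in intervention week 1 would remove the difficulty. Recommendations also go directly to the GP, so two weeks later there may be charted decisions to inspect. In addition, the Clinical Liaison Manager is charged with seeing that interventions are carried out as planned (section 2.4.3), and fidelity is sampled by discipline (section 2.11).

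The direct route cuts both ways, however. If the GP acts before the conference, the early visit has a purpose, but those changes are then the ones that Table 3 does not count.

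**Conclusion.** The point holds for the Table 3 outcome. As worded, it leaves out fall-risk medicine changes made through direct advice to the GP or at pharmacist visits, and no other listed outcome counts them. This rests on Tables 1 and 3 alone and does not depend on when the review is done. That some changes will arise by those routes is an inference from the planned contacts. The undercount cannot be estimated from the documents, and the 90% to 50% range only illustrates an assumed input.

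A reader might turn the 4 to 5 contacts into a statement that only 20% to 25% of changes are captured (1/5 to 1/4). That would be wrong. The documents do not call these contacts decision points, the two-week visit is described as a check on implementation, and a share of contacts is not a share of changes.

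The timing of the two-week visit is a secondary and conditional point. After a baseline review it will often come too early to check decisions agreed at the conference, but the review date is not stated and the visit could still check what the GP has already decided.

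This is a cheap improvement to a secondary process outcome. It does not touch the primary outcomes or the sample size, and the documents show neither bias in the main result nor a safety gap.

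**What to change.** **Main change, Table 3.** Redefine the outcome as the number of fall-risk medicines ceased or changed from the initial medication review to intervention week 36. Record the date of each change and its route: case conference, pharmacist follow-up, or direct to GP. Report the total and each route, so that the conference-only number remains available.

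**Conditional change, Table 1.** State the week of the initial medication review. If it lies in baseline, time the two-week visit from the case conference, so that it can check the decisions agreed there. Say that urgent medication concerns still go to the GP at once.

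**Cost.** The main change needs two extra REDCap fields, slightly more data entry, and the written ethics approval that section 4 requires for amendments. Moving the visit adds no visit and no staff, but a change that the GP makes before the conference would have its planned check later than now.
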